### Regulatory approvals

Ethics approval was obtained from South West – Central Bristol Research Ethics Committee in July 2016 (REC reference 16/SW/0154) and HRA approval in August 2016. Any protocol amendments will be submitted to the HRA for approval prior to implementation and updated on the ISRCTN registry.

### Patient involvement in trial design

Patients were involved in trial design through the University of Bristol’s Musculoskeletal Research Unit’s ‘Patient Experience Partnership in Research’ (PEP-R) patient involvement groups [32]. The PEP-R Musculoskeletal group comprises nine patients with musculoskeletal conditions, most of whom have had joint replacement. The PEP-R STAR group is a specialised group established for this programme of work, comprising five patients with experience of chronic pain after knee replacement. Both of these groups inputted into trial design, acceptability of randomisation, design of data collection and primary outcomes, questionnaires, patient information leaflets, recruitment consultations and qualitative topic guides.

### Patient recruitment

A diagram of participant flow in the trial is provided in Fig. 2.

**Fig. 2 Fig2:**
[figure not shown]
Participant flow through the trial

#### Eligibility criteria

Inclusion criteria are adults aged ≥ 18 years who have received a primary total knee replacement because of osteoarthritis at a participating NHS Trust and who report pain in their operated knee at 2–3 months after surgery, assessed using the 7-item pain subscale of the Oxford Knee Score (OKS) [35] (each item on the OKS is scored 0–4, with a total pain score of 0–28, severe pain to no pain). Based on previous cluster analysis [36], patients with pain are defined as those with a score of 0–14 on the OKS pain subscale.

Exclusion criteria are a lack of capacity to provide informed consent to participate, previous participation in the STAR trial for the contralateral knee, or participation in another research study that interferes unacceptably with the STAR trial.

#### Screening process to identify patients with chronic pain after knee replacement

An NHS employee will search hospital computer systems to identify all patients who had received a primary total knee replacement for osteoarthritis 2 months previously. These individuals will be sent a pre-screening notification card; 2–4 days later, they will be sent a screening study pack. Anonymised data on the age and sex of all patients sent a screening pack will be recorded. The screening pack includes a cover letter, patient information leaflet, screening questionnaire, a freepost envelope and a complimentary teabag. One reminder screening pack will be sent if no response is received within 1–2 weeks. Patients are asked to complete and return the screening questionnaire and consent form. On receipt of a completed screening questionnaire, the research team scores the OKS to identify patients with pain in their replaced knee (score of 0–14 on the OKS pain subscale).

#### Recruitment process

Patients who score 0–14 on the screening OKS pain subscale and consent to further contact from the research team will be posted a trial information pack and then telephoned by a researcher 3–5 days later. If participating, they will then complete a second OKS via telephone with the researcher to ensure they still meet the inclusion criteria for the trial. A face-to-face recruitment consultation at the participant’s home or local hospital is then arranged. Some of the final detailed aspects of this recruitment consultation will be informed by work during the pilot phase of the trial and will follow a model consultation process [37]. If a patient would like to participate in the trial, they will be asked to provide informed, written consent. All patients will be provided with a sheet of publicly available contact details for relevant charities or organisations, such as Arthritis Care, Pain Concern and Mind. Participants are then given a baseline questionnaire to complete and return to the research team. All researchers involved in recruitment have Good Clinical Practice and trial-specific training.

### Randomisation

After participants have provided written, informed consent and have returned a completed baseline questionnaire, they will be randomly allocated to the STAR pathway or usual care. Participants will be informed of their allocation by a member of the research team. Randomisation occurs as soon as possible after the baseline questionnaire is received. Randomisation with allocation concealment is conducted remotely via the Bristol Randomised Trials Collaboration using a web-based randomisation system. Randomisation takes place on a 2:1 basis to ensure that the intervention service is running at sufficient capacity to enable a pragmatic assessment of its clinical and cost-effectiveness. Moreover, if the intervention is operating to a sufficient degree of capacity, then per-protocol and Complier Average Causal Effect analyses will be more reliable and have higher power. To ensure reasonable balance between the two treatment groups, allocation is minimised by pain severity and pain interference scores for the replaced knee (assessed with the Brief Pain Inventory Severity and Interference Scales and categorised into tertiles based on data from a previous study [30]), and stratified by trial centre.

Blinding of participants and trial personnel to treatment allocation is not possible due to the nature of the intervention. After participants have been randomised, the research team will send the participant and their General Practitioner (GP) a letter to inform them of treatment allocation.

### Usual care

All patients in the trial receive usual care as provided by their hospital. The trial sites all provide a routine 6-week postoperative follow-up, and one centre provides an additional 3-month appointment. All centres provide additional follow-up with a surgeon if requested but do not include routine follow-up by practitioners specialising in pain.

### Intervention

Participants randomised to the intervention group will receive usual care and the STAR intervention, which consists of a 1-hour-long assessment clinic appointment with a trained Extended Scope Practitioner (a registered allied healthcare professional with specialist training in orthopaedics) and up to six telephone follow-up calls over 12 months (Fig. 3). Adherence to the intervention is defined as attendance at the assessment clinic appointment. Participants will be offered an assessment clinic appointment as soon as possible after randomisation, ideally within 1 week. Booking an appointment is arranged over the telephone and confirmed by letter.

**Fig. 3 Fig3:**
[figure not shown]
Schematic overview of STAR care pathway

The clinic appointment is booked for 1 hour and involves the Extended Scope Practitioner taking a clinical history, reviewing patient-reported outcome measures, conducting a knee examination, and reviewing radiographs and blood test results. Patient-reported outcome measures include the Brief Pain Inventory (BPI) [38], Hospital Anxiety and Depression Scale (HADS) [39], painDETECT [40] and Douleur Neuropathique 4 (DN4) [41]. The knee examination involves evaluating the sites and nature of knee tenderness, surgical wound healing, range of motion, alignment, stability, patellofemoral joint function, signs of infection, and signs and symptoms of Complex Regional Pain Syndrome as per the Budapest criteria [42]. A blood sample is taken to test for markers of infection. Participants have anteroposterior long leg alignment, lateral, and patella skyline knee radiographs taken if these have not already been performed as part of their usual care to evaluate alignment and assess for evidence of fracture or concerns with sizing, fixation or position of the implants. The appointment may last longer than 1 hour since additional time is required for radiographs.

Findings from the assessment clinic appointment are recorded on a standardised proforma and entered into the research database. On the basis of the STAR assessment, participants are referred to appropriate existing services for further treatment, which may include one or more of the following: a surgeon, when pain is attributable to surgical factors; physiotherapy for exercise and mobility advice and support; a GP for treatment of depression or anxiety; and/or pain specialists for neuropathic pain or Complex Regional Pain Syndrome (via GPs). Monitoring is also available if this is appropriate. The STAR care pathway is individualised and flexible, and other referrals can be made depending on the needs of the participant. Copies of all referral letters are sent to the patient, their treating orthopaedic surgeon and their GP.

Participants receive telephone follow-up from the Extended Scope Practitioner based on clinical need, up to a maximum of six times over 12 months. These telephone calls are to follow-up on the received and to ensure that any referrals are being undertaken. Additionally, further referrals can be made on the basis of these telephone follow-up consultations. Details of these telephone calls and any additional referrals made after the follow-up telephone call are documented on a standardised proforma.

All Extended Scope Practitioners delivering the intervention attend a 1-day training session and are provided with a comprehensive intervention training manual that includes standard operating procedures for the assessment. Further details of the development and content of the intervention, in line with the template for intervention description and replication (TIDieR) [43], has been published separately.

### Minimisation of contamination

It is possible that evolution of usual care over time may be influenced by implementation of the intervention at participating sites. To minimise this risk, we will liaise with the Principal Investigators and key trial staff at each site to ensure that information about the trial is disseminated to local clinical staff, taking care that this is not counterproductive. The provision of usual care will be monitored through resource use questions in the follow-up questionnaires at 6 and 12 months after randomisation.

### Co-treatments

Participants can seek treatment for related or unrelated medical conditions as needed during the trial. Use of health services are recorded in follow-up questionnaires and will be used in the health economics analysis.

### Assessment of intervention fidelity

Intervention fidelity evaluates the degree to which an intervention is delivered as intended [44]. In this trial, assessment clinics and telephone follow-up calls will be observed to evaluate if the intervention is being delivered as intended in the intervention training manual. A minimum of one assessment clinic for each Extended Scope Practitioner involved in intervention delivery will be observed annually. Observations are recorded on a standardised proforma and any additional training needs are highlighted and actioned.

### Outcome measurement

All participants are assessed at baseline prior to randomisation (3 months after surgery) and at 6 months (9 months after surgery) and 12 months (15 months after surgery) after randomisation. All outcome measurements will be undertaken via self-report questionnaires and participants are provided with a complimentary teabag with each questionnaire. Participants are offered the option of completing study questionnaires on paper or online through REDCap (https://www.project-redcap.org/). If completed questionnaires are not received within 2 weeks, a reminder questionnaire will be sent. If no response is received to the reminder, a researcher will telephone the participant to offer support in completing the questionnaire on the telephone. Telephone calls to participants who do not return a follow-up questionnaire will be performed by a researcher from a different trial centre to ensure that the researcher is blinded to treatment allocation.

The primary and secondary outcomes map directly onto the eight domains of the core outcome set for the assessment of chronic pain after knee replacement [45]. Details of the time point for each outcome are provided in Fig 1. The co-primary outcomes are pain severity and pain interference assessed using the BPI [38] at 12 months after randomisation. Participants will be asked to complete the BPI in relation to their operated knee. Secondary outcomes include:Pain and physical functioning: OKS [35]Neuropathic pain: PainDETECT [40] and DN4 [41]Psychological status: HADS [39], Pain Catastrophizing Scale [46], and Possible Solutions to Pain Questionnaire [47]Use of pain medications: Resource use questions (to be analysed as part of the cost-effectiveness analysis)Improvement and satisfaction with pain relief: Self-Administered Patient Satisfaction Scale [48], single-item question on comparison of pain to pre-operative painTemporal aspects of pain: Single-item questions on pain frequency during past 24 h and 4 weeks.Capability: ICECAP-A [49]Health-related quality of life: EQ-5D-5 L [50] and Short Form-12 [51]Pain elsewhere: body diagram to assess chronic widespread pain [52]

Mean/median scores at 12 months post randomisation will be analysed for continuous outcomes. The HADS and the single-item questions on pain frequency and comparison to pre-operative pain will be analysed as ordinal variables. Pain elsewhere will be treated as a dichotomous outcome, with patients defined as having chronic widespread pain if they report pain in at least two sections of each two contralateral limbs and in the axial skeleton.

The final questionnaire includes free-text questions that ask participants to explain what has and has not helped with their knee pain over the duration of the trial.

### Resource use

Resources used in relation to the intervention (including initial face-to-face assessment and telephone contacts) will be recorded on a standardised proforma. Use of health services including primary, secondary and tertiary care, use of personal social services and additional costs (private healthcare, travel, lost income, home modifications) will be collected in the follow-up questionnaires at 6 and 12 months after randomisation. Participants are provided with resource diaries and prescribed medication folders to prospectively record and document any health resources they have used to assist them in the completion of the questionnaires [53]. Resource use data, including inpatient stays and outpatient visits for all participants at the treating hospitals, will be obtained from hospital electronic systems or extracted from hospital records and recorded on a standardised proforma.

### Internal pilot phase

The 6-month internal pilot phase at four trial sites will evaluate patient identification and eligibility, recruitment rates, withdrawal rates and reasons for withdrawal, questionnaire completion rates, adverse reactions and protocol compliance. Embedded qualitative research, involving audio-recording of recruitment consultations and telephone interviews with participants, will be undertaken to optimise recruitment and trial processes. Anonymised transcripts from the recruitment consultations and interviews will be imported into the qualitative data management software QSR NVivo™. Data will be analysed thematically, involving inductive and deductive coding and categorisation [54]. Data from the pilot phase will be used to inform refinements to recruitment and trial processes. Patients recruited into the pilot phase will continue with the follow-up schedule and be retained in the full trial analysis.

### Safety

Data on adverse events reactions (adverse events directly attributable to the intervention) are collected and closely monitored to ensure the ongoing safety of participants. All serious adverse events will be notified to the study sponsor and reviewed by the Trial Steering Committee.

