### Data monitoring

The trial will be overseen by an independent Trial Steering Committee (TSC), composed of four clinical or non-clinical academics and one member of the public. The TSC will meet at regular intervals to review trial progress, protocol adherence and patient safety. The TSC decided that a Data Monitoring Committee was not necessary for this trial and that safety data and data quality will be reviewed by the TSC. No formal interim analysis will be conducted; however, data from the pilot phase were analysed to evaluate the feasibility of proceeding to the main trial. The trial will be stopped earlier than planned if mandated by the NHS Ethics Committee, recommended by the TSC, funding for the trial ceases or for any other relevant major clinical or therapeutic reason.

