## Appendix

**Table 1 Tab1:** World Health Organization Trial Registration Data Set

Item number	Item	Description
1	Primary registry and trial identifying number	ISRCTN92545361
2	Date of registration in primary registry	30/08/2016
3	Secondary identifying numbers	REC reference: 16/SW/0154 NIHR Programme Grant for Applied Research reference: RP-PG-0613-20,001
4	Sources of monetary or material support	NIHR Programme Grant for Applied Research
5	Primary sponsor	North Bristol NHS Trust Research and Innovation, [name] [contact] E-mail: [contact]
6	Secondary sponsor	Not applicable
7	Contact for public queries	[name] Musculoskeletal Research Unit, Translational Health Sciences, Bristol Medical School, University of Bristol [name] [contact] E-mail: [contact]
8	Contact for scientific queries	As above
9	Public title	Evaluation of a care pathway for patients with long-term pain after knee replacement
10	Scientific title	Evaluation of the clinical and cost-effectiveness of a care pathway for patients with chronic pain after total knee replacement: STAR trial
11	Countries of recruitment	UK
12	Health condition(s) or problem(s) studied	Chronic pain after total knee replacement
13	Intervention(s)	Intervention group: One-hour STAR assessment clinic with an Extended Scope Practitioner to identify potential causes of pain and enable onwards referral to appropriate existing services. Up to 6 telephone follow-up calls from the Extended Scope Practitioner over the 12 month follow-up period. Control group: Care as usual
14	Key inclusion and exclusion criteria	Age: 18 years or over; no upper age restriction Sex: Male or female Inclusion: Patients who have received a primary total knee replacement because of osteoarthritis at a participating NHS Trust and who report pain in their operated knee at 2–3 months after surgery (score of 0–14 on the Oxford Knee Score pain subscale). Exclusion: A lack of capacity to provide informed consent to participate, previous participation in the STAR trial for the contralateral knee, participation in another research study that interferes unacceptably with the STAR trial
15	Study type	Interventional Allocation: Randomised Assignment: parallel Phase III
16	Date of first enrolment	October 2016
17	Target sample size	381
18	Recruitment status	Recruiting

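### Apart from serious events, adverse events are collected only if directly attributable to the intervention, so non-serious harms have no usual-care comparator

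*Protocol article*

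**What the plan says.** The Safety section sets two rules. The first is the general one: "Data on adverse events reactions (adverse events directly attributable to the intervention) are collected and closely monitored". The second follows directly: "All serious adverse events will be notified to the study sponsor and reviewed by the Trial Steering Committee". The second rule has no attribution condition and is not limited to one arm.

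The Internal pilot phase section uses the narrower concept. Its list of items to evaluate includes "questionnaire completion rates, adverse reactions and protocol compliance" and names no other safety item.

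Only one arm is exposed. The Intervention section says "Participants randomised to the intervention group will receive usual care and the STAR intervention", and the registration table in the Appendix has "Control group: Care as usual". The Randomisation section says that participants and trial personnel cannot be blinded.

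Under Data monitoring there is no Data Monitoring Committee, and "safety data and data quality will be reviewed by the TSC". Outside the safety text, the Resource use section says "Resource use data, including inpatient stays and outpatient visits for all participants at the treating hospitals, will be obtained from hospital electronic systems", with manual extraction as the alternative source.

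**The concern.** The first rule makes attribution to the intervention a condition for recording an event, when attribution could be a judgement recorded alongside it. A usual-care participant cannot meet that condition. A non-serious event that would be recorded in the intervention arm, if judged attributable, goes unrecorded in the control arm even when it is the same event. The judgement is also made in an open trial, with allocation known.

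The nature of the intervention makes the judgement harder. The pathway consists of assessment followed by referral to existing services such as surgeons, physiotherapy and GPs. The article does not say whether an event arising from treatment after a referral counts as directly attributable. The full protocol may settle this, so it is not a separate fault. It does show how much rests on one unblinded judgement.

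What is at stake is the meaning of the safety statement in the final report. A low count of adverse reactions could be read as evidence that the pathway is safe relative to usual care. A higher count could be read as excess harm. For non-serious events, the collection rule supports neither reading.

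**Working it through.** **The plan's own figures.** The claim rests on no figure in the plan, but the arm sizes below come from the Sample size section.
- Inputs: 285 analysable participants, 2:1 allocation, differences of 0.35 to 0.40 SD, two-sided 5%, 25% loss, 381 recruited.
- Power with 190 against 95: the standard error in SD units is √(1/190 + 1/95) = 0.1257. At 0.35 SD, Φ(0.35/0.1257 − 1.96) = 79.5%. At 0.40 SD, 88.9%. These agree with the stated 80% to 90%.
- Inflation: 285/0.75 = 380, and 381 × 0.75 = 285.75. This agrees with 381 to within rounding.
- Arms as randomised: 381 × 2/3 = 254 intervention, 381 × 1/3 = 127 usual care.

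**The rules side by side.**

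| Type of event or record | Condition for capture | Can usual care contribute? |
|---|---|---|
| Adverse reaction (Safety, first rule) | Directly attributable to the intervention | No, barring cross-over |
| Serious adverse event (Safety, second rule) | None stated | Yes |
| Inpatient stay or outpatient visit at the treating hospital (Resource use) | None stated in that section | Yes |

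The structural zero therefore applies to the first row only. Serious events escape it through the second row. Non-serious events have no other route into the safety data as described.

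**Illustration of the distortion (assumed rates; the protocol gives none).** Let a proportion p of each arm have a non-serious event, with no true difference, and let a fraction f of those in the intervention arm be judged directly attributable. Expected recorded counts are 254 × p × f in the intervention arm and 0 in usual care.

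| p | f = 10% | f = 30% |
|---|---|---|
| 5% | 1.3 | 3.8 |
| 10% | 2.5 | 7.6 |
| 20% | 5.1 | 15.2 |

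The recorded contrast runs from about 1 to about 15 events of 254, against 0 of 127, while the true difference is zero.

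**What a by-arm table of serious events could show (assumed rates).** If 5% of each arm had an event, the 95% half-width for the risk difference would be 1.96 × √(0.05 × 0.95 × (1/254 + 1/127)) = 4.6 percentage points. The power of a two-sided 5% test would be 26% for 2% in usual care against 5% in the intervention arm, 37% for 5% against 10%, and 71% for 10% against 20%. The table would serve estimation and oversight, and could not exclude modest differences.

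**The case against.** A reader might infer that no harms of any kind can be compared, and that the usual-care arm is zero for everything, including death, re-operation and readmission. The documents do not support that. All serious adverse events are notified and reviewed with no stated attribution or arm limit, and hospital stays and visits are obtained for all participants. The steering committee is therefore not left with adverse reactions alone. How serious events are ascertained in each arm is not described, but an article may leave that to the full protocol.

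Three further objections have force.
- **By-arm safety tables belong in the analysis plan.** The article says that a full plan exists. This stands, so the absence of a table here is not the fault. The fault is the capture rule, which the article does state and which an analysis plan cannot undo: events that were never collected cannot be tabulated.
- **Limiting collection of non-serious events can be a reasonable choice in a pragmatic trial of a care pathway.** Pain, function, neuropathic symptoms and mood are measured in both arms by questionnaire, so some kinds of worsening will be seen. This stands too. It is why a plainly stated limitation is an acceptable alternative to changing the definition.
- **A table of serious events and hospital episodes recovers no non-serious event in the control arm.** This is correct. The table is a useful addition but does not close the gap, so the fix has two separate parts.

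**Conclusion.** The point holds for adverse events below the serious threshold. Under the stated rule, the expected recorded count in about 127 usual-care participants is zero whatever their true rate, so these harms cannot be compared between arms. The conclusion assumes that usual-care participants do not cross over to the pathway and that the full protocol does not define the events differently. It does not extend to serious adverse events, nor to outcomes visible in hospital records.

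The 1 to 15 recorded events in the illustration depend entirely on the assumed rates; only the control-arm zero comes from the document. No sample size, power or significance level changes. The consequence is for the interpretation of the safety results, and the remedy is cheap enough to be worth making.

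**What to change.** 1. Keep adverse-reaction reporting, and choose one of two courses for non-serious events. Either define and ascertain them in the same way in both arms, with attribution recorded as a separate item, or state in the plan and the report that adverse-reaction counts describe the intervention arm and are not a comparison.
2. Add a by-arm table, regardless of attribution, of deaths, serious adverse events, and knee-related readmissions and re-operations, with risk differences and 95% confidence intervals. Its sources are the serious-event reports and the hospital records obtained for all participants. Provide it to the Trial Steering Committee.
3. Confirm the scope of the hospital extraction. The Cost-effectiveness analysis section limits measured resources to those used in treating chronic pain. If that limit also governs the extraction, some knee-related episodes could be filtered out by a relatedness judgement before they reach the table.

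Cost: the stated limitation in step 1 costs a sentence, whereas the common definition needs equal ascertainment in both arms. Step 2 uses sources the protocol already describes and needs some extra coding of hospital episodes, a little more if step 3 shows that the extraction must be widened. Intervals for rare events will be wide and should be presented as such.
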